### Withdrawal criteria

Parents will be considered withdrawn from the study if they refuse to participate or fail to undergo post-intervention evaluation. Reasons for participant withdrawals and discontinuation within the trial will be documented.

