Emerging studies have demonstrated that health education based on self-efficacy theory has been effective in increasing parental self-efficacy and improving disease management outcomes for parents of children with chronic diseases (27–29). For example, Cheng et al. (27) designed a randomized controlled trial (RCT) based on the self-efficacy theory for parents in controlling child’s eczema, which showed significant improvement in the child’s eczema severity and parental self-efficacy. Similarly, another RCT was conducted for parents of children with asthma, the intervention groups had significantly higher parental self-efficacy and 1.4 times the child’s experience of an asthma crisis improved compared to the control group post-intervention (da Rocha Mendes et al., 2024). However, non-significant results were also observed, an online platform was developed to enhance parental self-efficacy and of parents with a child with type 1 diabetes, the self-empowerment was not significant change post-intervention (30).

In summary, most existing ASD parents program emphasize knowledge or skills delivery (10), but relatively few have been designed primarily to enhance parental psychological such as PSE, or to target Bandura’s four sources of self-efficacy in a structured way (3). Therefore, this intervention will address the gap by testing whether a theory-driven, nurse-delivered PSE intervention improves parental self-efficacy, parenting stress, family quality of life and symptom severity post intervention and at 6-month follow-up. The hypotheses are as follows:

Compared with the control group, the intervention group will be expected to demonstrate higher parental self-efficacy scores at post-intervention and at 6-month follow-up.Compared with the control group, the intervention group will show higher improvements in secondary outcomes at post-intervention and at 6-month follow-up, including lower parenting stress, higher treatment compliance, family quality of life, and reduced child symptom severity.

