### Data collection

The researcher will recruit parents by posting posters during the first two days of hospitalization. Eligible parents will undergo a thorough explanation of the study, and written consent will be obtained (-T1) by researchers. Two nurses trained in using standardized instructions will collect the data. Baseline data (T0) will be collected face-to-face using a paper version of the questionnaire. Post-intervention data will be collected within three days after intervention (T1) and 6 months after the intervention (T2) through the online questionnaire platform, *Questionnaire Star* (Changsha Ranxing Information Technology Co., Ltd). This platform was chosen for its ability to ensure data quality, provide an opt-out option, and allow parents to complete the surveys at their convenience. The flow diagram of the trial procedures is presented in **Figure 2**.

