### Statistical methods

IBM SPSS 26.0 (IBM Corp., NY, USA) will be used for data analysis. Descriptive statistics such as mean, median, standard deviation, interquartile range, frequency, and percentage will be used to describe the baseline characteristics of the participants. The independent *t*-tests and one-way ANOVA will be used to compare the homogeneity of the two groups at baseline. Outcome analyses will be conducted based on the intention-to-treat (ITT) principle. Missing data will be imputed based on the results of Little’s missing completely at random (MCAR) test. The generalized estimating equations (GEE) model will be used to analyze the group and time differences in outcome variables. Potential covariates such as sociodemographic or clinical characteristics with a *P<*0.01 in the baseline will be considered in the adjusted GEE model. Open-ended contents will be summarized descriptively with selected anonymized quotations. Statistical significance will be set at 0.05 (two-sided).

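### The withdrawal rule treats a missed T1 assessment as leaving the study and is not reconciled with the ITT, imputation and GEE commitments

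*Protocol article*

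**What the plan says.** Under Withdrawal criteria the protocol article fixes the rule: "Parents will be considered withdrawn from the study if they refuse to participate or fail to undergo post-intervention evaluation". The section then asks only that the reasons be recorded, and it gives no further consequence of being withdrawn.

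Table 1 (Study design) heads the T1 column as the post-intervention measurement and the T2 column as the follow-up measurement. Data collection gives the timing: "Post-intervention data will be collected within three days after intervention (T1) and 6 months after the intervention (T2"). Both are completed on an online questionnaire platform.

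The Statistical methods section commits to three things. The first is the analysis principle: "Outcome analyses will be conducted based on the intention-to-treat (ITT) principle". The second is imputation of missing values, with the approach depending on Little's MCAR test. The third is the model: "The generalized estimating equations (GEE) model will be used to analyze the group and time differences in outcome variables".

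The primary hypothesis, at the end of the Introduction, expects "higher parental self-efficacy scores at post-intervention and at 6-month follow-up". The secondary hypothesis names the same two time points.

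**The concern.** Under intention-to-treat, a missed questionnaire is missing data at one visit and does not end participation. The Withdrawal criteria merge the two. Two consequences are possible.

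The first is lost follow-up. A parent recorded as out of the study after missing T1 would ordinarily not be sent the T2 form. Both hypotheses include T2, the form is online, and the Preparation phase text sets up WeChat groups in both arms partly to reduce loss to follow-up. The rule works against that effort and forgoes data that the GEE could use.

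The second is an ambiguous analysis set. An analyst could take *withdrawn* to mean *not analysed* and work only with parents who completed T1. If those who miss T1 differ from those who complete it, and differ by arm, the group comparison would be biased at both time points.

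**Working it through.** **1. Which assessment triggers the rule.** Table 1 ties the post-intervention label to T1 alone. Data collection uses post-intervention data for T1 and T2 together. T1 is the more natural reading. On either reading, missing an outcome assessment is classed as withdrawal.

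**2. What follows from the label.** The Withdrawal criteria require reasons to be documented. They do not say that withdrawn parents leave the analysis, lose their T0 data or are no longer approached at T2. The Statistical methods section does not say how a withdrawn parent enters the ITT analysis. The two sections are therefore unreconciled, but they do not state opposite things.

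**3. Whether the imputation sentence settles it.** It does not. Parents who complete T1 but miss T2, or who skip items, would need imputation even if everyone missing T1 were dropped. The sentence fits both a full ITT set and a completer-at-T1 set.

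**4. How many parents could be affected.** Inputs from Sample size: 40 per group, 15% dropout, SD 0.76, 80% power, two-sided alpha 0.05.

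- Evaluable per group: 40 × (1 − 0.15) = 34, and 34 / 0.85 = 40, so the dropout allowance is consistent with 40 per group.
- The section states no target difference, so the sample size cannot be reproduced from its inputs. Solving backwards by the normal approximation gives 0.76 × √(2/34) × (1.960 + 0.842) = 0.516, or 0.68 SD. The t-based value is 0.524, or 0.69 SD.
- Planned dropout: 40 × 0.15 = 6 per arm, 12 of 80 overall. This covers loss for any cause, so it is a ceiling-type scale and not an estimate of the rule's effect.

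**5. Ceiling on lost precision at T2.** Under the back-solved difference of 0.516 (an assumption), 34 per arm gives 80.0% power and a fully observed 40 per arm gives 86.0% (78.8% and 85.1% by t). The rule's own share of that gap is limited to parents who miss T1 but would have answered T2. The documents do not give that number.

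**6. Illustration of bias if withdrawn parents are left out.** Assume that the 6 lost intervention parents would score *k* SD below completers and that control loss is unselective. The documents give no value for *k*.

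- Bias = 0.15 × *k*. For *k* = 0.8 this is 0.12 SD; for *k* = 0.5 it is 0.075 SD.
- Standard error of the difference = √(2/34) = 0.243 SD.
- For *k* = 0.8 the shift in z is 0.12 / 0.243 = 0.49. The two-sided false-positive rate is P(Z > 1.96 − 0.49) + P(Z < −1.96 − 0.49), about 0.071 + 0.007, or roughly 8%.
- Relative to the back-solved 0.69 SD, 0.12 / 0.69 = 17%.

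These figures hold only if all planned dropout falls under the rule, all of it is excluded, and selection acts in one arm only.

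**The case against.** The strongest reply is that being withdrawn and being excluded from analysis are different things, and the article states only the first. It commits to ITT with imputation, and an article may leave the definition of the analysis set to a fuller document. This stands against two stronger readings that a reader might infer: that the rule contradicts the ITT statement, and that it converts the analysis into a completer analysis. Neither is in the text. It does not remove the point, because the withdrawal rule is a stated rule and not an omission, and as worded it turns one missed form into an end of participation.

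A reader might also infer that refusal to participate is a route out mainly for the intervention arm, which has four sessions to decline. The documents do not support this. The rule speaks of refusing to participate, not of refusing sessions, and controls can refuse questionnaires too. Adherence is recorded separately under Acceptability. Refusal before consent raises no ITT issue, since "Eligible parents will undergo a thorough explanation of the study, and written consent will be obtained (-T1) by researchers" comes ahead of baseline. Refusal after consent is the ordinary right to withdraw.

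Finally, the bias illustration does not measure the harm of this sentence. A parent who misses T1 has no T1 score whatever label is applied, and the fix recovers none. This objection stands in full.

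**Conclusion.** The concern holds in a limited form. The Withdrawal criteria class a missed post-intervention evaluation as withdrawal from the study, and this is not reconciled with ITT, imputation and a repeated-measures GEE. Taken literally, the rule forgoes T2 data from parents who miss T1 but could answer at 6 months. It permits a completer-at-T1 analysis set without prescribing one.

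The documents do not allow the bias to be sized. Six parents per arm is an upper scale resting on the planned 15% dropout. The 0.12 SD and 8% figures are arithmetically correct but apply only under the exclusion and selection assumptions set out above. An inflated benefit at T1 and T2 should not be claimed as a demonstrated result of the rule. The point rests on the text and merits correction because the remedy is cheap.

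**What to change.** Replace the withdrawal sentence and add one to Statistical methods, to this effect:

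- Withdrawal means withdrawal of consent.
- A missed T1 is missing data, and non-attendance at sessions is recorded under adherence.
- T2 is sought from every parent who has not withdrawn consent, whether or not T1 was completed.
- All enrolled parents are analysed in their assigned cohort with all available T0, T1 and T2 data, including T2 data from parents who missed T1.

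The cost is two or three sentences, and the T2 form and the WeChat groups already exist. Study setting and population dates the study from October 2022 to May 2024. If collection has closed, the T2 element can no longer be changed. The analysis-set statement can still be fixed before analysis, and the report should give, by arm, how many parents missed T1 and whether T2 was sought from them.

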### Interventions

#### Preparation phase

A nurse-led intervention team was established, consisting of nursing specialists specialized in pediatric nursing, nursing postgraduate students in pediatric nursing orientation, pediatricians, rehabilitation therapists, and senior clinical nurses experienced in ASD intervention. The nursing postgraduate students and specialists developed an initial intervention protocol, which was based on the results of the literature review and Bandura’s self-efficacy theory. Then, the second version of the protocol was validated by one pediatrician and three senior clinical nurses with extensive experience in ASD intervention.The pamphlet for “Family Training for Children with ASD” was formulated by the intervention team members. The pamphlet covers five aspects: understanding ASD, the importance of parents in early family intervention, integrating intervention into daily life, daily management of the child, and parental emotional management. It also includes a daily intervention record sheet for parents to document their intervention activities and note any challenges. Contact information for the department and nurses is provided in the pamphlet. In **Figure 1**, the screenshots of the pamphlet are shown.To facilitate communication and minimize follow-up loss, WeChat (Tencent Corp) accounts and separate WeChat groups will be created for both the experimental and control groups. WeChat, the most popular communication software in China, was chosen for its convenience and accessibility. These groups will be managed by nursing graduate students, providing a convenient way to contact parents. The WeChat groups will also be utilized to send session links (for the experimental group) and collect information from parents during the follow-up period (for both groups).

**Figure 1 f1:**
[figure not shown]
Screening shot of pamphlet.

#### Control group

Parents in the control group will receive routine care, including nursing care such as toilet instruction, feeding instruction and sleep instruction provided during hospitalization. Nurses will follow up with parents through telephone calls one, two, or three months after discharge.

#### Intervention group

Parents in the intervention group will receive the parenting self-efficacy (PSE) program and routine care. A pretest involving four parents was implemented prior to the start of the intervention. The final protocol includes a total of four sessions: one face-to-face session before discharge and three online sessions at weeks 1, 2, and 3 post-discharge. Each session will last 40–60 minutes. Intervention delivery will follow a hybrid method: an in-person session during hospitalization for *in-situ* coaching, followed by three online sessions via Tencent Meeting after discharge to maintain continuity and reduce travel burden.

The first session will take place in the hospital’s meeting room before participants are discharged. The nurse will introduce herself, describe the intervention process, invite parents to join the intervention group’s WeChat group and provide a pamphlet. A PowerPoint presentation on “understanding ASD” and “the importance of parents in early family intervention” will be delivered. Subsequently, the nurse and a rehabilitation therapist will collaborate with parents to set individualized goals and content for home training based on their child’s specific needs. Lastly, parents will be instructed to complete a training record sheet to document daily training activities and reflections. The remaining three online sessions will be conducted via Tencent meetings. The second session will focus on strategies for integrating intervention into daily life and family management. The third session will focus on emotion management in the care giving process of children with ASD. The nurse and rehabilitation therapist will discuss the child’s intervention process, address challenges faced by parents in implementing and adhering to the intervention, assess achievements, and provide support in problem-solving and enhancing confidence in the intervention. In the fourth session, the nurse and parents will review the initial goals set by parents, assess progress and challenges encountered in adhering to the intervention, and discuss new goals or encourage persistence in implementing efforts. Within the group, 1–2 parents who have a proactive attitude toward the intervention and are willing to share their caring experiences may be invited to do so. They will provide insights and tips based on their experiences to facilitate learning and discussion among parents. With parental consent, a video demonstrating the parents implementing intervention for a child with ASD may be shown to inspire learning and discussion among parents. These four aspects are incorporated into each component of the intervention, as shown in **Table 2**.

**Table 2 T2:** Parental self-efficacy promotion components, strategies, and techniques.

Components	Strategies	Content
Mastery experience	Setting achievable goals Providing information on ASD Gaining experience	(1) Based on the previous assessment (PEP-3) and behavior observation, the intervention team will work with parents to develop intervention goals and identify achievable goals for their child at home training. (2) Teaching the knowledge about ASD and family training. (3) Emphasize the importance of family intervention, and encourage parents to record the daily training content.
Vicarious experience	Experience sharing from other parents	(1) Inviting some parents to share their experience of caring for children. (2) Watching 1–2 videos of parents training their children at home. Encourage parents to learn and discuss with each other.
Verbal persuasions	Verbal encouragement, explanation, and persuasion throughout the process	(1) Give timely recognition to parents who persist in intervention to negative emotions, and encourage them to continue to do so. (2) When parents do not adhere to the intervention and encounter difficulties, help them to find out the reasons, propose countermeasures, and encourage them to adhere to home training.
Physical and affective states	Mobilizing positive emotions	(1) Mental health education: parents are instructed to manage their emotions during the caring process of children, and guide parents to seek help from psychologists if necessary. (2) Encourage parents to talk to their friends and relatives when they encounter difficulties. And encourage parents to pay more attention to their physical situations. (3) Play a 5-minute medication video about relaxation and breathing.
	Providing social support	(1) Mobilize family members to learn about the intervention and encourage family members to participate in the intervention, and create a friendly family atmosphere. (2) Provide relevant resources and introduce domestic support policies, and information on intervention services and institutions. (3) Encourage parents to promptly reflect on any questions in the WeChat group during the follow-up phase to help them solve questions.

### Data collection

The researcher will recruit parents by posting posters during the first two days of hospitalization. Eligible parents will undergo a thorough explanation of the study, and written consent will be obtained (-T1) by researchers. Two nurses trained in using standardized instructions will collect the data. Baseline data (T0) will be collected face-to-face using a paper version of the questionnaire. Post-intervention data will be collected within three days after intervention (T1) and 6 months after the intervention (T2) through the online questionnaire platform, *Questionnaire Star* (Changsha Ranxing Information Technology Co., Ltd). This platform was chosen for its ability to ensure data quality, provide an opt-out option, and allow parents to complete the surveys at their convenience. The flow diagram of the trial procedures is presented in **Figure 2**.

**Figure 2 f2:**
[figure not shown]
Flow diagram of the trial procedures.

### Data management

To protect the confidentiality of participants, all data will be de-identified using participant codes before analysis. De-identified data will be stored on a password-protected hard disk (encrypted external drive). Access is role-based and restricted to authorized team members (PI, data manager, statistician). Data will be retained for 10 years after publication, then securely destroyed. In line with registry requirements, de-identified data will be uploaded to the ResMan (http://www.medresman.org) within six months of publication. Additional access will be available from the corresponding author upon reasonable request.

### Outcomes

#### Sociodemographic characteristics

The parents’ and their children’s sociodemographic characteristics will be collected by a self-designed questionnaire. It includes the parents’ age, sex, marital status, education level, employment status, per capita monthly income, the number of children in the family, living status, and the children’s age, sex, and education status.

#### ASD-related characteristics

Participants will be asked about the ASD-related characteristics of their child, including the child’s age at the first observed ASD-related symptoms, initial ASD-related symptoms observed by the parents, comorbid conditions, the age at ASD diagnosis, presence or absence of ASD-related training, monthly expenditure for training and payments for training expenses, presence or absence of family training, the child’s age at first presence of family training, the frequency of family training, clinic outpatient visits or not, self-reported major factors affecting the presence of intervention.

#### Primary outcome

Parental self-efficacy will be measured using the Chinese version of the Parenting Sense of Competence Scale (C-PSOC) (33). The 6-point rating scale comprises a 17-item and assesses satisfaction and efficacy across two dimensions. Scores range from 17 to 102, with higher scores indicating higher levels of parenting self-efficacy. The C-PSOC has demonstrated high internal consistency and reliability (34).

#### Secondary outcomes

Parenting stress will be measured using the Parenting Stress Index-Short Form (PSI-SF) (35). This questionnaire comprises 36 items and three subscales, namely parenting distress, dysfunctional parent-child interaction, and characteristics of children with difficulties. The questionnaire uses a 5-point Likert scale, ranging from 36 to 180, with higher scores indicating higher levels of parenting stress. The PSI-SF has high reliability and validity (36).

Treatment compliance of parents of children with ASD will be assessed using the Treatment Compliance Scale for Children with Autism Spectrum Disorder (37). The scale consists of two subscales, namely medication compliance (optional) and rehabilitation treatment compliance. This scale employs a 5-point Likert scale, ranging from 1 (never) to 5 (always). The total score ranges from 18 to 110, and when medication items were excluded, the score ranges from 18 to 90. With higher scores indicating better compliance. The scale has good validity and reliability (37).

The family’s quality of life will be measured using the Chinese version of the Beach Center Family Quality of Life Scale (BCFQoL) (38). This 25-item, 5-point Likert scale assesses FQoL across five domains from importance and satisfaction ratings from 1 (not at all important/dissatisfied) to 5 (very important/very satisfied). A higher score indicates a greater level of agreement with the importance or satisfaction of the FQoL. The scale has good reliability and validity (39).

The Chinese version of the Autism Behavior Checklist (ABC) (40) is used to assess parents’ perceptions of the severity of children. The ABC includes 57 items with five dimensions, which are sensory, relating, body and object use, language, and social and self-help, with higher scores indicating greater symptom severity. The cut-off scores for ASD screening and diagnosis were 31 and 62, respectively. The scale has good reliability and validity (41).

